**Secondary endpoints:**

The measurement instruments are described under ‘Measurement Instruments’.

1. Severity of posttraumatic stress symptoms (PCL-5, 6-item version)
2. Presence and severity of suicidal ideation (SIDAS)
3. Self-identified problems (PSYCHLOPS)
4. Wellbeing (WHO-5)
5. Psychological Flexibility (adapted CompACT & AAQ-II)
6. Repetitive Negative Thinking (PTQ-Short Form)
7. Intolerance of Uncertainty (abbreviated IOUS)
8. Social satisfaction and functioning (abbreviated WHOQoL-BREF items and SAS-SR-modified)
9. Physical health (abbreviated WHOQoL-BREF)
10. Post-Migration Living Difficulties (adapted PMLD Checklist)
11. Exposure to adverse life events (adapted HTQ)
12. Use of emotion regulation strategies (adapted RESS-EMA)
13. Momentary emotions
14. Functional impairment (WHODAS-12)

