Participants deemed eligible based on the online screener and phone screener process will be invited to participate in the trial and sent a link to review the trial’s Participant Information Statement and Consent Form. Following informed consent, participants will be contacted to book their first assessment (Structured Assessment 1). Structured Assessments will be conducted by trained research assistants called ‘Assessors’ (see ‘Trial Personnel’ below) and will involve the administration of the scales in a structured interview format to assess mental health and psychosocial functioning (see ‘Measurement Instruments’ below). If, at the time of the baseline assessment (Structured Assessment 1), the participant’s symptoms of psychological distress have spontaneously improved such that they no longer score above the cut-off, they will be provided feedback on their test outcomes and it will be explained why they are no longer eligible for the study.

After the baseline assessment, participants will be randomized on a 2:1 (active treatment : waitlist control) basis by an independent research assistant, not involved in the assessments, using computerized software. Participants will be randomised to either the Active Treatment condition (*n*=214) or the Waitlist Control condition (*n*=107) to form a single-blind waitlist control RCT design. Participants in the Active Treatment condition will receive the 5-week DWM intervention from Weeks 1-5. Regardless of condition, all participants will complete Structured Assessments every 3 weeks.Upon completion of the final Structured Assessment (1-month follow-up, conducted 9-weeks following baseline assessment), participants in the Waitlist Control condition will gain access to the DWM workbook and audio files.

The instruments administered in Structured Assessments 2-4 closely resemble those used in Structured Assessment 1, with minor changes (as some scales do not need to be re-administered). This is outlined in the ‘Measurement Instruments’ section below. In case participants do not attend a scheduled assessment, the research team will attempt to contact them via follow-up text messages and/or phone calls for a maximum of eight times for scheduling a new appointment.

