Participants in both conditions will also complete two 1-week ecological momentary assessment (EMA) blocks, initiated the day following pre-treatment assessment and again following post-treatment assessment (in week 6). At the end of Structured Assessment 1 (pre-treatment), assessors will explain the EMA process and guide participants in downloading and setting-up the Avicenna application on their smart phone. The participant and assessor will then complete a practice survey together. The next day, the participant’s 7-day block will commence. At five random times between 10am and 10pm each day, participants will receive notifications to complete a 1-2 minute survey on their phone. This procedure will be repeated in week 6, following the completion of Structured Assessment 3 (post-treatment). During an EMA block, if participants miss 2 or more of the 5 daily surveys, they will be contacted (either via text message or call) to check whether the participant is experiencing any issues (such as technological difficulties) that the team can assist with to support full participation.

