Acceptance and Action Questionnaire-II (Hayes et al., 2004) will be used to assess psychological inflexibility over the past week. The scale comprises 7 items (on a 7-point Likert scale). Higher scores indicate higher levels of psychological inflexibility characterized by greater experiential avoidance. This scale has been extensively used in the literature, including randomized controlled trials with forcibly displaced people (Acarturk et al. 2022; Lakin et al., 2023). The psychometric properties of the scale were reported excellent (Ong et al., 2024).

*Emotion Regulation*

In the current study, emotion regulation will be assessed using an ecological momentary assessment (EMA) paradigm, which will involve two 1-week EMA blocks (each comprising 5 ultra-brief surveys per day for 7 days). Each survey will comprise 21 items in total: nine items assessing momentary emotional states (e.g., anger, sadness, relaxation; adapted from Cloos, Ceuleman & Kuppens., 2023), eight items assessing momentary emotion regulation strategy use (e.g., rumination, suppression, acceptance; adapted from the Regulation of Emotion Systems Survey-EMA version; Medland et al., 2020), and 4 items assessing momentary stressors (e.g., positive event, negative event, event unpleasantness/pleasantness; adapted from Baik & Newman, 2023). Items are scored on a 0-100 sliding scale. An EMA paradigm, using similar items, have been employed with refugees (Koch et al., 2020).

*Repetitive Negative Thinking*

The short form of the Perseverative Thinking Questionnaire (PTQ) (Ehring et al., 2011) will be used to measure to which extent participants are impacted by negative repetitive thinking over their problems on a 5-point Likert Scale (0 = Never, 4 = Almost Always). The short form (Moeller et al., 2023) consists of 9 items tapping into three subscales: core feature and unproductiveness of repetitive negative thinking, and mental capacity captured by it. Higher scores indicate higher levels of repetitive negative thinking. The scale has previously been used in several studies, including randomized controlled trials with trauma-exposed populations (Heckendorf et al., 2019).

*Intolerance of Uncertainty*

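### Randomisation is tied to Structured Assessment 1, not to the end of the 7-day EMA block that follows it, so the only EMA baseline can be collected after participants know their allocation

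*Protocol*

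**What the plan says.** All of the timing is in the protocol's section 10.1 (Trial Intervention), unless noted.

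- **EMA.** "Participants in both conditions will also complete two 1-week ecological momentary assessment (EMA) blocks, initiated the day following pre-treatment assessment". The same sentence goes on to date the second block: "initiated the day following pre-treatment assessment and again following post-treatment assessment (in week 6"). At the end of SA1 the assessor sets up the app, and then: "The next day, the participant’s 7-day block will commence". The Measurement Instruments section gives the density: "each comprising 5 ultra-brief surveys per day for 7 days".
- **Randomisation.** "After the baseline assessment, participants will be randomized on a 2:1 (active treatment : waitlist control) basis". The same section uses baseline assessment as another name for SA1. No day is given for randomisation, for telling participants the result, for sending the workbook or for the first facilitator call.
- **Treatment.** "Participants in the Active Treatment condition will receive the 5-week DWM intervention from Weeks 1-5". Day zero of Week 1 is not defined.
- **Follow-up.** Structured Assessments are 3 weeks apart, and the last is the "1-month follow-up, conducted 9-weeks following baseline assessment". Section 10 (introduction and The Control Condition) places this last assessment at the end of a 9-week waitlist period.
- **Use of the EMA data.** The secondary endpoints include "Use of emotion regulation strategies (adapted RESS-EMA") and momentary emotions. Emotion regulation is also a hypothesised mechanism under Aim 2.
- **Blinding.** The Trial Design section blinds outcome assessors only.

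**The concern.** There are only two EMA blocks, so the first is the sole baseline for emotion regulation strategies and momentary emotions. A baseline should precede allocation. Here the trigger for randomisation is SA1, and the EMA week begins the day after SA1. A participant who already knows that support is starting, or that a 9-week wait lies ahead, may rate emotions and coping differently and may answer prompts more or less often. Assessor blinding gives no protection, because participants enter EMA responses on their own phones.

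The Statistics section applies the primary outcome's mixed model, with the baseline value as covariate, to secondary outcomes. Its examples do not name the EMA measures. If the first block is used in that way, or as the starting point of a change score, any early shift caused by allocation is treated as a pre-existing difference and part of the effect may be removed. Completion of the first block could also differ by arm.

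**Working it through.** No sample-size formula applies. The check is a day count with SA1 as day 0.

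**1. Reproduce the protocol's own timeline.** Assessments every 3 × 7 = 21 days fall on days 0, 21, 42 and 63. The last is at 63 / 7 = 9 weeks, as stated.

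**2. Place the EMA blocks.** Block 1 starts the day after SA1 and lasts 7 days: days 1 to 7, with 5 × 7 = 35 surveys. Block 2 follows SA3 on day 42: days 43 to 49 if it starts the next day.

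**3. Place allocation.** Randomisation follows SA1, with no upper limit stated. The waitlist period lasts 9 weeks and ends at the final assessment on day 63, so it begins on day 63 − 63 = 0, which is SA1. On that count block 1 lies wholly inside the waitlist period. If allocation is made and disclosed promptly after SA1, 35 of 35 surveys come after it. This step does not depend on how weeks are numbered.

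**4. Overlap with DWM Weeks 1 to 5.** This does depend on the numbering.

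| Convention | DWM days | EMA block 1 days in Week 1 | Block 2 days in week 6 |
|---|---|---|---|
| Ordinal: week k = days 7(k−1)+1 to 7k | 1 to 35 | 7 of 7 | 0 of 7 |
| Elapsed: week k = days 7k to 7k+6 | 7 to 41 | 1 of 7 (5 of 35 surveys) | 6 of 7 |

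Under ordinal weeks, with the first call on day d, the surveys on or after that day number 5 × (8 − d): 35 of 35 for d = 1, and 5 of 35 for d = 7. The protocol puts block 2 in week 6, which fits elapsed weeks and not ordinal ones. The protocol's own label therefore favours little or no overlap with sessions.

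**5. Can treatment wait for block 1 without moving the assessments?** Purely as an illustration, five weekly calls beginning on day 8 fall on days 8, 15, 22, 29 and 36. The last is 42 − 36 = 6 days before SA3 and 63 − 36 = 27 days before SA4, close to 4 weeks.

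**The case against.** The strongest reply is that the protocol dates neither randomisation nor the first DWM contact. Randomising after SA1 sets only an earliest point, and the two schematics, which are not available here, may show the EMA week coming first. This is fair, and it rules out saying that the baseline is in fact collected after allocation. It does not remove the gap: the prose ties the trigger to SA1, and the waitlist counts back to the same day.

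Three stronger readings are tempting and are not supported.

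- **That the EMA baseline is partly collected during treatment.** This requires Week 1 to mean days 1 to 7. The week 6 label points to elapsed weeks, with at most one shared day.
- **That a follow-up one month after treatment and a visit 9 weeks after baseline can both hold only if DWM occupies days 1 to 35.** If DWM is counted as days 8 to 42, the gap is 63 − 42 = 21 days, but that counts a full week after the fifth call as treatment. Measured from a fifth call on day 36, it is 27 days.
- **That the effect is attenuated by a stated percentage.** Any such figure needs an assumed early shift and an assumed baseline slope, and the protocol gives neither. Nor would attenuation of a between-arm contrast carry over directly to Aim 2, which rests on a per-protocol cross-lagged analysis within the intervention.

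**Conclusion.** The point holds in a limited form. In the visible text nothing keeps the only EMA baseline ahead of allocation, and the 9-week waitlist suggests that allocation comes first. Up to 35 of 35 first-block surveys can be given by unblinded participants who know their arm. The full 35 assumes that allocation is made and disclosed promptly after SA1. Overlap with DWM sessions ranges from none, if the first contact waits for the block to end, to 7 of 7 days, and is not established.

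The consequence is confined to the two EMA secondary endpoints and the EMA measure of emotion regulation. Its size cannot be derived from the protocol. The K10 baseline is taken at SA1, before randomisation, so the primary analysis is untouched. This is a cheap improvement worth making before recruitment, since an EMA baseline collected after allocation cannot be retrieved by analysis.

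**What to change.** In section 10.1:

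- State that randomisation, or at least disclosure of allocation and release of the DWM materials, takes place only after EMA block 1 has closed. Randomising after the block is the better of the two, because losses during that week then precede allocation.
- Define day zero of Week 1, so that the DWM weeks, the week 6 label and the 9-week visit use one count.
- Keep the Structured Assessments at 3, 6 and 9 weeks after SA1. Renumbering them from the end of the block is unnecessary: it would put the last visit about 10 weeks after SA1 and contradict the stated 9 weeks.
- Say that the 9-week waitlist is counted from SA1.

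The cost is wording and a changed randomisation trigger. There would be about one week between SA1 and allocation, so the K10 baseline and the eligibility re-check at SA1 would be about a week old at allocation. A few participants may be lost in that week. If they leave before randomisation this does not bias the comparison; if only disclosure is delayed, they remain randomised and count in the intention-to-treat set.

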# **Trial Objectives and Purpose**

**Aim 1:** To evaluate the *efficacy* of Doing What Matters in Times of Stress (DWM) – a low-intensity mental health intervention – for refugees displaced in Indonesia.

- The hypothesis to be tested is that DWM (DWM workbook + five weekly facilitator sessions) will decrease psychological distress compared to a waitlist control group.

**Aim 2:** To evaluate the *mechanisms* underlying Doing What Matters in Times of Stress (DWM) – a low-intensity mental health intervention – for refugees displaced in Indonesia.

- The hypothesis to be tested is that reductions in psychological distress during and after the provision of DWM will be mediated by improvements in key psychosocial processes (psychological flexibility, emotion regulation, intolerance of uncertainty, and social functioning).

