**Measurement Instruments:**

The instruments used to assess and monitor mental health and psychosocial functioning are outlined in the below table.

|  | **When measure is administered** | | | | |
| --- | --- | --- | --- | --- | --- |
| **Construct & Measure** | **Screener** | **Structured Assessment 1** | **Structured Assessments 2-4** | **Ecological Momentary Assessment** | **DWM sessions** |
| Demographics | X | X |  |  |  |
| Psychological Distress (K10)* | X | X | X |  |  |
| Posttraumatic Stress Reactions (PCL-6) |  | X | X |  |  |
| Suicidal Ideation (SIDAS) |  | X | X |  |  |
| Self-Identified Problems (PSYCHLOPS) |  | X | X |  |  |
| Wellbeing (WHO-5) |  | X | X |  |  |
| Psychological Flexibility (adapted CompACT & AAQ-II) |  | X | X |  |  |
| Repetitive Negative Thinking (PTQ- Short form) |  | X | X |  |  |
| Intolerance of Uncertainty (abbreviated IoUS) |  | X | X |  |  |
| Social Satisfaction and Functioning (abbreviated WHOQoL-BREF items and SAS-SR-modified) |  | X | X |  |  |
| Physical Health (abbreviated WHOQoL-BREF) |  | X | X |  |  |
| Post-Migration Living Difficulties (adapted PMLD Checklist) |  | X | X |  |  |
| Perceived benefit (newly adapted items) |  |  |  | X |  |
| Adverse Life Events (adapted HTQ) |  | X |  |  |  |
| Digital Markers** |  | X | X |  |  |
| Momentary Emotions and Stressors |  |  |  | X |  |
| Emotion Regulation Strategies (RESS-EMA) |  |  |  | X |  |
| Treatment fidelity (checklists) |  |  |  |  | X |
| Treatment contamination check |  | X | X | X |  |

*Psychological Distress (K10) is the primary outcome measure

**Digital Markers are measured in Structured Assessments 1 and 3 only.

*Screener and Primary Outcome Measure*

*Psychological Distress*

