# **Statistics**

Data collected throughout the study will be analysed using hierarchical linear modelling or linear mixed models. Both intention-to-treat analysis (ITT; using all randomised participants) and completers’ (PP) analysis will be used.

Primary study parameters:

The main conclusion for study aim 1 (testing the efficacy of the DWM intervention, according to K10 scores) will be based on the ITT analysis of the primary outcome. A secondary analysis of the primary outcome will also be presented using the PP population. To estimate the treatment effect, data from Structured Assessments 1-4 will be used. A linear mixed model will be employed for the primary endpoint analysis, which will have treatment as fixed effects, baseline measurement of primary endpoint as covariate, and subject as random effects. The mean difference between two treatment arms at each visit/time together with its 95% confidence interval will be derived from the mixed model. Covariate-adjusted mixed model of primary endpoint will also be performed by adding pre-specified covariates at baseline (gender, age, education, traumatic experiences, and severity of symptoms) into the above model.

- Secondary study parameters: A linear mixed model as mentioned for the primary outcome analysis will be carried out for analysing the secondary outcomes (e.g., PTSD, Suicidal Ideation, Self-Identified Problems, Wellbeing, Functional Impairment, Digital Markers).

The main conclusion for study aim 2 (testing the mechanisms of change within the DWM intervention) will be based on the PP analysis, to ensure that only data from participants who received a sufficient ‘dose’ of the intervention are analysed. Cross-lagged panel analysis will be used to determine the temporal sequencing of psychological factors over the course of the intervention period, to test whether the hypothesised processes were mechanisms of change driving the intervention effects [hypothesis 2].

- The hypothesised mechanisms are: psychological flexibility (primary), emotion regulation, social satisfaction and functioning, and intolerance of uncertainty.

Missing data: Missing data will be treated as missing at random (MAR). No imputations of missing values will be made, as multilevel models can deal with missing data (Singer & Willett, 2003).

Other study parameters:

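### The planned cross-lagged analysis cannot place change in emotion regulation before the K10 during treatment, because emotion regulation is measured only in an EMA block after baseline and another after the post-treatment assessment

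*Protocol*

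**What the plan says.** Hypothesis 2 (Trial Objectives and Purpose) is that "reductions in psychological distress during and after the provision of DWM will be mediated by improvements in key psychosocial processes", and emotion regulation is among the processes named there.

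The Statistics section sets the analysis: "Cross-lagged panel analysis will be used to determine the temporal sequencing of psychological factors over the course of the intervention period". It then lists what is to be tested: "The hypothesised mechanisms are: psychological flexibility (primary), emotion regulation, social satisfaction and functioning, and intolerance of uncertainty". It makes no exception for any of the four.

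Under Measurement Instruments, "emotion regulation will be assessed using an ecological momentary assessment (EMA) paradigm, which will involve two 1-week EMA blocks". The schedule table in that section agrees: the RESS-EMA row is marked in the EMA column only, with nothing under Structured Assessments 1 to 4. The instruments for the other three listed mechanisms are marked at all four assessments.

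Section 10 (Trial Intervention) gives the timing: both arms complete "two 1-week ecological momentary assessment (EMA) blocks, initiated the day following pre-treatment assessment and again following post-treatment assessment (in week 6"). The same paragraph adds that the second block comes once SA3 has been completed.

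The K10 is taken at all four Structured Assessments. These are three weeks apart, and the last is nine weeks after baseline.

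**The concern.** A cross-lagged panel supports a claim about mechanism when a change in the mediator is observed before the change in outcome that it is meant to explain. For three of the four listed mechanisms the schedule allows this, because mediator and K10 are recorded together on four occasions. For emotion regulation there is no mid-treatment value, and the only value after the first block is collected after the post-treatment K10.

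An analyst who applies the plan to all four mechanisms has two options during treatment. One is to pair the second EMA block with SA3 as if they were a single wave, which puts the mediator after the outcome. The other is to use the first block alone, which tests whether an early level predicts later distress. Neither tests the hypothesis, which concerns improvement. The trial chose 2:1 allocation to support aim 2 (Trial Design, Sample Size), so a mis-ordered mediation claim would fall on something the design was built to deliver.

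**Working it through.** The check is one of timing. The protocol gives no figure to reproduce.

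**Inputs**
- K10 occasions: SA1 to SA4, three weeks apart, the last nine weeks from baseline (section 10). 3 intervals × 3 weeks = 9 weeks, so the occasions fall at about weeks 0, 3, 6 and 9 (days 0, 21, 42 and 63).
- EMA block 1: seven days from the day after SA1, so days 1 to 7.
- EMA block 2: seven days, after SA3. If it starts the day after SA3, as block 1 does after SA1, it covers days 43 to 49 and ends at week 49 / 7 = 7. The starting day is an assumption; the order relative to SA3 is stated.
- EMA content: momentary emotions, regulation strategies and stressors (Measurement Instruments). The K10 is not among the items.

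**What emotion-regulation information exists before each K10**

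| K10 occasion | Week | Emotion regulation already measured | Change in emotion regulation already measured |
|---|---|---|---|
| SA1 | 0 | none | no |
| SA2 | 3 | block 1 (early level) | no |
| SA3 | 6 | block 1 (early level) | no |
| SA4 | 9 | blocks 1 and 2 | yes |

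**Counts**
- K10 occasions after baseline and up to post-treatment: 2 (SA2, SA3). Preceded by a measured change in emotion regulation: 0 of 2.
- K10 occasions after baseline overall: 3. Preceded by a measured change: 1 of 3 (SA4).
- Gap from the end of block 2 to SA4: 63 − 49 = 14 days.

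**The two directions are not equally covered.** K10 at SA1, SA2 and SA3 all precede block 2, so paths from distress to later emotion regulation can be estimated across the treatment period. The hypothesised path, from changed emotion regulation to later distress, cannot be estimated within that period.

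**Dense sampling does not help.** Each block has 5 × 7 = 35 prompts, 70 in total. They allow lags between strategies and momentary emotions within a week. But no block falls at mid-treatment, so they say nothing about change before the K10 at SA2 or SA3.

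**The case against.** The strongest reply is that emotion regulation can still be tested with correct time order. Hypothesis 2 covers the period after treatment as well as during it, and block 2 precedes the K10 at SA4. That stands. It rules out a stronger reading that a reader might reach, that any result for emotion regulation would be uninterpretable. A partial test of the after-treatment component remains. Lagged paths from block 1 to K10 at SA2 and SA3 also exist, but they use an early level and not a change.

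A second reply is that model details belong in the statistical analysis plan, which is not shown. That is true of covariates and estimation. It does not dispose of the point, because the protocol itself fixes the measurement times, the type of analysis and the list of mechanisms. No analysis plan can supply a mid-treatment value that was not scheduled.

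Two further inferences are tempting and are not supported.
- **Block 1 overlaps the first week of DWM, so the estimated change is diluted.** Section 10 says "Participants in the Active Treatment condition will receive the 5-week DWM intervention from Weeks 1-5", but does not date the first session relative to SA1. With SA3 at day 42 and 35 days of treatment, 42 − 35 = 7 days are unaccounted for, exactly the length of block 1. Overlap is possible but not shown, so no attenuation can be claimed. The protocol attaches the term pre-treatment to SA1 and does not call the block itself pre-treatment.
- **Repetitive negative thinking should take the place of emotion regulation.** It is described among the hypothesised mechanisms and measured at SA1 to SA4, yet is absent from hypothesis 2 and from the list in the Statistics section. That is a small inconsistency, unrelated to EMA timing. It is a separate construct, and whether to add it to the hypothesis is the sponsor's choice.

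**Conclusion.** The point holds in a limited form. As written, the Statistics section applies a test of sequencing during the intervention to four mechanisms, and for one of them the scheduled data cannot support it. No change in emotion regulation can be placed before the K10 at SA2 or SA3 (0 of 2); one of the three post-baseline K10 measurements, SA4, can follow such a change.

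This rests on the stated order of block 2 and SA3 and on EMA being the only emotion-regulation measure. It does not depend on the exact calendar days.

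A reader might infer that aim 2 as a whole fails. The documents do not support that: psychological flexibility, intolerance of uncertainty and the social measures have four waves each. Aim 1 is not touched.

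**What to change.** In the Statistics section:
- Exclude emotion regulation from the cross-lagged panel covering the intervention period, and state that no claim about sequencing during the intervention will be made for it. Hypothesis 2 should carry the same limit so that the two sections agree.
- Pre-specify the remaining time-ordered test: emotion regulation in EMA block 2 predicting K10 at SA4, adjusted for block 1 and for K10 at SA1 and SA3. The SA3 adjustment is needed because that K10 precedes block 2 and may influence both block 2 and the K10 at SA4.
- Run it in the analysis set that the section already defines for aim 2 (per protocol). If both arms are used, adjust for arm and state that this departs from the per-protocol basis.

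This is a change of wording and analysis only, with no new data. The cost is a narrower claim for emotion regulation, limited to change in distress between week 6 and week 9. If the sponsor wants to keep the during-treatment claim, it would need a mid-treatment EMA block or a brief emotion-regulation scale at the Structured Assessments, which adds participant burden.
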